Parents of infants born preterm may experience a range of responses following the birth, including depression [24-27], anxiety [28-30] and symptoms of post traumatic stress disorder[31]. Studies have also shown that parental stress is related to less sensitive, more intrusive and more active maternal interactional behavior[32]. There is some evidence that programs that are aimed at improving the parent-child interaction through providing emotional support in the way of information and education of infants' behavioral cues, encouragement and empathy increased parental feelings of self confidence and competence, and increased positive parent-infant interaction [33-35]. The study by Dolby et al[6] used the three phases of attachment development described by Sroufe above [22] to guide their intervention program.

Whilst the program by Dolby et al[6] has a strong theoretical background, the methodology (study design and subject numbers) and reporting of the results limits the conclusions that can be drawn from the study. Therefore, we conducted a randomized controlled trial, partly based upon the theoretical content of the Dolby et al[6] study, with the aim of improving the infant's motor and cognitive performance, the parent-infant relationship, and primary caregiver mental health outcomes. The original intervention model reported by Dolby et al[6] which was created in the 1980s, has been updated in the present intervention to account for current theories of development and research on early intervention[3]. In addition, this intervention targets very preterm infants who have been identified as being at high risk for developmental impairment. The VIBeS Plus program was designed for infants born at younger gestational ages (all infants will be born at <30 weeks' gestational age whereas the mean gestational age of the Dolby study infants was 32 weeks), with a higher incidence of multiple births, and with the study commencing later, at 40 weeks' gestation rather than before 40 weeks in the NICU. We have published a Cochrane review of early developmental interventions that demonstrated that interventions commencing post hospital discharge had similar effects on cognitive and motor development compared with interventions that commenced in the NICU[3]. The theoretical framework for the VIBeS Plus program incorporates the theoretical models used in the study by Dolby et al[6] with the inclusion of dynamic systems theory and family centered practice model.

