### Randomization Process

Infants will be randomly allocated to the intervention and control groups by a computer-generated random sequence, with the treatment allocation concealed in opaque envelopes; only the trial statistician will have access to the code. As parents have the choice to participate in the study without their infant undergoing brain MRI, there will be three strata: 1) nil to mild white matter abnormality, 2) moderate to severe white matter abnormality, or 3) no-MRI group. Secondly, as infants of multiple births need to be randomized to the same group due the family being involved in the intervention, there will also be stratification for multiple births.

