### Analysis plan

Analysis will follow standard principles for randomized controlled trials, using simple two-group comparisons performed using all subjects for whom outcome data are available, on an intention-to-treat basis. The primary comparison at 24 months will be based on the Bayley cognitive and motor composite scores, which will be compared between groups using linear regression, controlling for multiple births. Multivariate regression will be used to adjust for potential imbalances in major baseline confounders such as the extent of brain injury (and sociodemographic variables). Secondary analyses will use similar methods to compare the outcomes between groups for the additional motor (NSMDA, AIMs); behavioral (ITSEA), primary caregiver mental health and parent -child interactions measures (VIBES, EAS) at 24 months. For dichotomous outcomes, comparisons will be by chi-squared tests and where continuous data exhibit substantial skewness, non-parametric (Mann-Whitney U test) methods will be used for simple comparisons, and regression analyses performed after appropriate transformation of the outcome.

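### The chi-squared and Mann-Whitney tests named in the plan treat siblings as independent, although multiples are allocated together, so their p-values are too small if siblings' outcomes are positively correlated

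*Protocol article*

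**What the plan says.** All references are to the protocol article.

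- **Allocation.** Under Randomization Process, "infants of multiple births need to be randomized to the same group due the family being involved in the intervention". For multiples, the family is therefore the unit of allocation. The Background, under Attachment Theory, describes this sample as one "with a higher incidence of multiple births" than the earlier study on which the program is partly based. It gives no percentage.
- **Primary analysis.** Under Analysis plan, the Bayley scores are to be "compared between groups using linear regression, controlling for multiple births".
- **Secondary analyses.** The same section continues: "Secondary analyses will use similar methods to compare the outcomes between groups".
- **Named simple tests.** "For dichotomous outcomes, comparisons will be by chi-squared tests". For continuous outcomes, "where continuous data exhibit substantial skewness, non-parametric (Mann-Whitney U test) methods will be used for simple comparisons", with "regression analyses performed after appropriate transformation of the outcome".

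No cluster-adjusted form of either simple test is mentioned.

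**The concern.** The standard chi-squared and Mann-Whitney tests take their null variance from independent observations. Two siblings in the same arm whose outcomes are alike carry less information than two unrelated infants. The tests then understate the variance of the group difference, and the p-value comes out too small. The plan recognises multiples in its primary regression, but these two tests have no place for a covariate or a family cluster.

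The outcomes most exposed are those shared within a family. Under Outcome Measures, HADS, PSI-SF and SSQ are completed by or about the primary caregiver, and IOF-G and FAD describe the family. If such a score were attached to each twin's record, the two entries would be the same observation. At stake is the error rate of unadjusted, mainly secondary comparisons. The skewness sentence is worded for continuous data in general, so it is not strictly confined to secondary outcomes.

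**Working it through.** **1. The plan's own figure.** Sample Size Calculations uses 0.4 SD (6 points, so SD 15), alpha 0.05 and 80% power. Two-sided, for independent infants, n per arm = 2 × (1.96 + 0.8416)² / 0.4² = 98.1, so 99. The stated 100 per group reproduces, with power 0.807 at 100. This fixes the setting used below: 200 infants and a nominal 5% test. The point does not alter the stated N.

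**2. Inputs the documents do not give.** The share m of infants in twin pairs is assumed to be 0.2 to 0.4. The within-pair correlation ρ is assumed to be 0.3 to 1.0. Higher-order multiples are left out.

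**3. Formula.** A singleton contributes variance factor 1. An infant in a same-arm twin pair contributes 1 + ρ. Averaged over infants, the design effect is (1 − m) × 1 + m × (1 + ρ) = 1 + mρ. A test that ignores this rejects with true probability 2 × [1 − Φ(1.96 / √(1 + mρ))].

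**4. Results.** Each cell shows the design effect, then the true type I error.

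| m | ρ = 0.3 | ρ = 0.5 | ρ = 1.0 |
|---|---|---|---|
| 0.2 | 1.06, 0.0569 | 1.10, 0.0617 | 1.20, 0.0736 |
| 0.3 | 1.09, 0.0605 | 1.15, 0.0676 | 1.30, 0.0856 |
| 0.4 | 1.12, 0.0640 | 1.20, 0.0736 | 1.40, 0.0976 |

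The effective size of 200 infants runs from 200 / 1.06 = 189 to 200 / 1.40 = 143.

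**5. Check by simulation of the tests themselves.** Settings: 10,000 null trials each, 100 infants per arm, lognormal outcome, twins in the same arm, uncorrected chi-squared with a 20% event rate.

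| m | ρ | Mann-Whitney | Chi-squared |
|---|---|---|---|
| 0 | none | 0.053 | 0.051 |
| 0.2 | 0.5 | 0.063 | 0.055 |
| 0.3 | 0.5 | 0.070 | 0.063 |
| 0.4 | 0.5 | 0.074 | 0.061 |
| 0.2 | 1.0 | 0.076 | 0.075 |
| 0.3 | 1.0 | 0.081 | 0.085 |
| 0.4 | 1.0 | 0.094 | 0.100 |

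Without twins both tests sit at about 5%, so the excess comes from siblings. Here ρ is set on the underlying normal scale. Dichotomizing weakens it, which is why chi-squared is less affected at ρ = 0.5.

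**6. Does a clustered analysis cure it?** A second simulation used 6,000 null trials per setting and 200 infants, with families randomized within strata of multiple birth.

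| m | ρ | Mann-Whitney | Chi-squared | Family-clustered regression |
|---|---|---|---|---|
| 0.3 | 0.8 | 0.076 | 0.072 | 0.049 |
| 0.3 | 1.0 | 0.084 | 0.089 | 0.051 |
| 0.4 | 0.8 | 0.085 | 0.076 | 0.054 |
| 0.4 | 1.0 | 0.096 | 0.104 | 0.052 |

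The Monte Carlo standard error at 5% is √(0.05 × 0.95 / 6,000) = 0.003, so the clustered regression is at nominal within simulation error.

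**The case against.** The strongest reply has four parts.

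- **The plan keeps regression for secondary outcomes.** It does: secondary analyses follow the primary method, and skewed outcomes are also regressed after transformation. For continuous outcomes, only the accompanying simple test lacks the control. This narrows the point but does not remove it, because a promise of similar methods cannot repair a test that has no means of adjusting. For dichotomous outcomes no regression is named beside the chi-squared test. Control for multiple births entered only as a covariate would not handle within-family correlation either. The article does not say which is meant.
- **A fuller analysis plan could supply cluster-adjusted tests.** It could, but one that followed this text would run the tests named here.
- **The size is uncertain and the comparisons are mostly secondary.** Both stand. Outcome Measures also designates no dichotomous endpoint; the HADS bands are described, not set as an outcome.
- **Double-counting of caregivers is conjecture.** That stands too. A reader might infer that each caregiver is entered once per twin, but the text does not say so.

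A reader might also infer that the analyst may choose between a rank test and a transformed regression once results are seen. The Analysis plan does not support that: it gives the rank test to simple comparisons and the transformation to regression analyses. A cut-off for skewness and the choice of transformation are details commonly left to the statistical analysis plan, and no harm from leaving them open has been shown. A rank test for a skewed score is legitimate in itself; the fault is only that its standard form ignores siblings.

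**Conclusion.** The point holds as a defect of independence. Multiples are allocated together, and the two simple tests named in the Analysis plan cannot take account of it. Followed as written, they give p-values that are too small whenever siblings' outcomes are positively correlated.

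Under assumed twin shares of 20% to 40% and correlations of 0.3 to 1.0, the true type I error of a nominal 5% test is about 5.7% to 9.8%. For child outcomes at a correlation of 0.5 it is about 6.2% to 7.4% by formula. It would be wrong to read the upper figures as the expected error for all secondary outcomes. They need a correlation near 1, which means a shared score entered once per infant. With few multiples or weak correlation the inflation is small.

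**What to change.** - **Dichotomous outcomes:** replace the chi-squared test with logistic regression or GEE, clustered by family.
- **Substantially skewed continuous outcomes:** base inference on a regression with family-clustered robust intervals, or with bootstrap intervals that resample families. A cluster-adjusted rank test is an alternative. Any ordinary Mann-Whitney test becomes a sensitivity analysis.
- **Caregiver and family outcomes:** state that each caregiver contributes one record.

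This is a change of wording in the analysis plan, with standard regression options and no new data. The downside is slightly larger p-values for some secondary outcomes.

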## Discussion

This paper outlines a preventative care program designed for preterm infants over the first year of life to improve motor, cognitive and behavioral development. The program is based upon theoretical models and includes components of previously successful interventions. It is designed to be feasible to implement in a community setting, and to be able to be generalized across different groups in Australia and internationally. This study provides a unique opportunity to determine if a preventative care program will improve motor, cognitive, and behavioral outcomes at two years of age, as well as caregiver mental health.

## Abbreviations

EPDS: Edinburgh Postnatal Depression Scale; CISS: Coping Inventory for Stressful Situations; IOF-G: Impact of Family Scale; STAI: State Trait Anxiety Inventory; PSI: Parenting Stress Index; WMI: white matter injury; BSITD-III: Bayley Scales of Infant and Toddler Development -3^rd ^edition; AIMS: Alberta Infant Motor Scale; NSMDA: Neurological Sensory Motor Developmental Assessment; ITSEA: Infant Toddler Social Emotional Assessment; HADS: Hospital Anxiety and Depression Scale; PSI-SF: Parenting Stress Index - Short Form; SSQ: Social Support Questionnaire; FAD: Family Assessment Device.
